# Flexor Injury Rehabilitation Splint Trial (FIRST): protocol for a pragmatic randomised controlled trial comparing three splints for finger flexor tendon repairs

**DOI:** 10.1186/s13063-024-08013-z

**Published:** 2024-03-16

**Keywords:** Finger flexor tendon rupture, Finger flexor tendon repair, Rehabilitation, Splinting, Hand therapy, Physiotherapy, Occupational therapy, Surgery, Randomised controlled trial

## Abstract

**Background:**

Without surgical repair, flexor tendon injuries do not heal and patients’ ability to bend fingers and grip objects is impaired. However, flexor tendon repair surgery also requires optimal rehabilitation. There are currently three custom-made splints used in the rehabilitation of zone I/II flexor tendon repairs, each with different assumed harm/benefit profiles: the dorsal forearm and hand-based splint (long), the Manchester short splint (short), and the relative motion flexion splint (mini). There is, however, no robust evidence as to which splint, if any, is most clinical or cost effective. The Flexor Injury Rehabilitation Splint Trial (FIRST) was designed to address this evidence gap.

**Methods:**

FIRST is a parallel group, superiority, analyst-blind, multi-centre, individual participant-randomised controlled trial. Participants will be assigned 1:1:1 to receive either the long, short, or mini splint. We aim to recruit 429 participants undergoing rehabilitation following zone I/II flexor tendon repair surgery. Potential participants will initially be identified prior to surgery, in NHS hand clinics across the UK, and consented and randomised at their splint fitting appointment post-surgery. The primary outcome will be the mean post-randomisation score on the patient-reported wrist and hand evaluation measure (PRWHE), assessed at 6, 12, 26, and 52 weeks post randomisation. Secondary outcome measures include blinded grip strength and active range of movement (AROM) assessments, adverse events, adherence to the splinting protocol (measured via temperature sensors inserted into the splints), quality of life assessment, and further patient-reported outcomes. An economic evaluation will assess the cost-effectiveness of each splint, and a qualitative sub-study will evaluate participants’ preferences for, and experiences of wearing, the splints. Furthermore, a mediation analysis will determine the relationship between patient preferences, splint adherence, and splint effectiveness.

**Discussion:**

FIRST will compare the three splints with respect to clinical efficacy, complications, quality of life and cost-effectiveness. FIRST is a pragmatic trial which will recruit from 26 NHS sites to allow findings to be generalisable to current clinical practice in the UK. It will also provide significant insights into patient experiences of splint wear and how adherence to splinting may impact outcomes.

**Trial registration:**

ISRCTN: 10236011

**Supplementary Information:**

The online version contains supplementary material available at 10.1186/s13063-024-08013-z.

## Background

### Background and rationale {6a}

#### The personal and economic burden resulting from finger flexor tendon injuries

Hand injuries in the UK have increased by 57% in 15 years, accounting for 20% of emergency presentations [1]. There were 7346 flexor tendon injuries in 2018–2019; 75% were in working age men [2]. Such injuries most frequently occur from a direct laceration to the tendon in the finger or palm of the hand. Without surgical repair and rehabilitation, divided tendons do not heal; patients cannot bend fingers, grip objects, or effectively care for themselves and others. Long-term prognosis can be poor: 50% of patients report pain and functional limitations 10 years post-injury [3].

#### Flexor tendon repair requires optimal rehabilitation, but the evidence base is limited

The outcome of flexor tendon surgery relies on effective rehabilitation [4]. Patients routinely attend weekly appointments for up to 3 months after surgery, with full recovery (when achieved) taking up to 1 year [5]. There are two components to rehabilitation: exercises to prevent hand stiffness and promote tendon glide/excursion and the provision of a splint to protect the repair.

In the UK, there are three main custom-made splints used in the rehabilitation of zone I/II flexor repairs; however, there is insufficient evidence to inform the efficacy of these splints. A systematic review comparing rehabilitation following flexor tendon surgery suggested that future high-quality randomised controlled trials were required to establish which rehabilitation regimes are safe and most effective [6].

### Long—forearm and hand-based splint

A survey of UK current practice used to inform the feasibility of FIRST found that the long splint is the most commonly used splint following flexor tendon repairs. This has been the mainstay of clinical practice in the UK since the 1980s. This splint protects the newly repaired tendons by preventing movement at the wrist and reducing extension of the fingers.

### Short—hand-based splint

This was developed to allow combined wrist and finger movement and is believed to reduce the risk of complications such as stiffness, fixed flexion deformities of the interphalangeal joints (IPJs), and tendon adhesions due to the increased excursion of the repaired tendons through the synergistic motion of the wrist and hand. This has been reported in a case-series comparing the short and long splint for zone I/II flexor repairs [7]. Our recent survey showed that the short splint has been incorporated into rehabilitation regimes for zone I/II repairs in approximately 50% of hand centres across the UK.

### Relative motion flexion splint (Mini)—finger-based splint

Over the last 5 years, there has been a worldwide shift in the management of extensor tendon repairs moving from using a long splint to the relative motion extension splint (RMES) [8]. More recently, the concept of relative motion splinting has also been introduced into clinical practice for flexor tendon repairs. The relative motion flexion (RMFS (mini)) splint positions the affected digit into relative flexion and therefore utilises the quadriga effect to reduce the biomechanical pull on the repaired tendon. It is also worn in combination with a wrist splint for the first 3 weeks in order to limit full extension of the wrist. The mini splint is thought to provide less protection than the long and short splints described above, but the patients’ function may be improved whilst wearing the splint. This may lead to reduced joint stiffness.

### Rationale for current trial

Patients and clinicians need to know if one splint provides superior outcomes in terms of pain and function: this is the main justification of conducting this RCT. The process evaluation will help us understand how patient-level factors moderate adherence and how adherence mediates benefit and harm outcomes, which is critical for decision-making. Economic evaluation is essential because, while splint costs are comparable and relatively small, the costs of treatment failure and reintervention are substantial. The trial will be conducted in accordance with the protocol and the International Conference on Harmonisation (ICH) Good Clinical Practice (GCP).

### Objectives {7}

#### Aims

The aim is to investigate the clinical and cost-effectiveness of three splints, and mediators of effectiveness, in the repair of zone I/II finger flexor tendons to determine superiority.

#### Objectives

To determine if any splint is superior in terms of a patient-rated measure of pain and functionTo investigate how patient values and splint acceptability moderates objectively measured splint adherence and how adherence mediates effectivenessTo evaluate splint cost-effectiveness, from an NHS and societal perspective

### Trial design {8}

This is a parallel group, three-arm, superiority, analyst-blind, multi-centre, individual participant-RCT.

Consenting participants will be randomised to receive either the long splint, short splint, or mini splint. Outcome data will be collected at 6, 12, 26, and 52 weeks post-randomisation.

An 8-month internal pilot will assess the feasibility of the RCT. The progression criteria will be applied to data collected 8 months after the first site is opened. The progression criteria (see Table 1) will be assessed by the trial steering committee (TSC) at the end of the following month.

**Table 1 Tab1:** Progression criteria

Criterion	Red (% complete)	Amber (% complete)	Green (% complete)
Number of Sites opened	< 15 (75%)	> = 15 (75%) and < 20	20 (100%)
Rate/site/month	< 0.9 (< 60%)	> = 0.9 (60%) and < 1.4	1.5 (100%)
Number of participants recruited	< 144 (< 60%)	> = 144 (60%) and < 240	240 (100%)
Allocation per protocol	< 90%	> = 90% and < 100%	100%
% FU (% of recruited)	< 50%	> = 50% and < 75%	75%

## Methods: participants, interventions, and outcomes

### Trial setting {9}

Participants will be recruited from outpatient hand clinic/therapy services in 26 NHS hospitals across the UK. The hospitals are a mix of city, regional, and teaching hospitals and include a range of sizes (8 large: > 100 flexor tendon injuries treated a year; 7 medium: 50–100 treated a year; 11 small: < 50 treated a year). See Additional file 1 for details of all 26 hospitals.

### Eligibility criteria {10}

#### Inclusion criteria

In order to be eligible for the RCT, the following criteria must all be met at the point of randomisation:Participants aged 16 or overPrimary repair of zone I/II finger flexor tendonSurgical repairs according to BSSH guidelines for flexor tendon repairs

#### Exclusion criteria

Patients who meet the following criteria will not be eligible for the RCT:Patients with associated fractures requiring fixation or additional splintageTendon lacerations involving 3 or more fingersRevascularisation surgery and/or digital nerve reconstructions requiring a nerve graftPresented for treatment more than 3 weeks following the original injuryPatients unable to consent or comply with the rehabilitation regime, for example, due to cognitive, psychological or physical disabilitiesCurrently enrolled in another hand trial

### Who will take informed consent? {26a}

#### Participant identification

Patients listed for a planned repair of zone I/II finger flexor tendon, or who have recently undergone surgical repair of zone I/II flexor tendons, will be identified by delegated site staff and provided with a participant information sheet (PIS).

Following surgery, all patients routinely receive a standard care appointment with hand therapy, where decisions regarding their treatment and splint provision are made. Recruitment to the RCT will therefore be aligned with this appointment. Site staff will explain the RCT procedures and answer any questions the patient may have. Prior to consent, eligibility will be confirmed by the research team by completing an eligibility form.

All patients who are approached about the RCT will be recorded on an anonymised screening form with non-identifiable data. Where patients are not interested in the RCT, or are ineligible following surgery, this will be recorded on the screening form.

At RCT set up, an Equality Impact Assessment will be conducted to ensure all patients have equal opportunity to take part. The best practice guidance from The Centre for Black and Minority Ethnic (BME) Health will also be applied.

### Informed consent process

The site research team will confirm patients’ eligibility post-surgery by completing an eligibility form. Eligible patients will be invited to consent to the RCT at their first-hand therapy appointment post-surgery. They will have already been provided with the PIS and will have had time to consider their potential participation. If they are happy to proceed, written consent will be recorded at the clinic visit. Instances where potential participants decline consent will be recorded on an anonymised screening form within the case report form (CRF). Where given, reasons for declining consent will be recorded.

Participant information sheets and consent forms will be translated into approximately seven different languages. Non-English-speaking participants will be given access to an interpreter if required, to answer any questions they may have.

#### Additional consent provisions {26b}

Separate consent will be taken for the qualitative interviews. With patient consent, FIRST qualitative researchers will have access to contact details for the purposes of contact for the qualitative study. Selected participants will be sent an additional information sheet via email. With permission, informed consent will be recorded verbally over video call, at the time of interview by the researchers.

## Interventions

### Explanation for the choice of comparators {6b}

This pragmatic RCT will assess the three main custom-made splints currently used in the rehabilitation of zone I/II flexor repairs: long forearm and hand-based splint, short hand-based splint, and mini finger-based splint.

### Intervention description {11a}

For each type of splint, the splint will be fitted at the first-hand therapy appointment post-surgery.

#### Patients randomised to long splint

The forearm-based early active motion splint, or ‘long splint’, is a custom-made, thermoplastic splint which allows controlled early active movement. It covers the dorsal aspect of the whole hand and forearm, thereby preventing motion of the wrist and allowing for controlled motion of the fingers. The long splint will be prescribed for 5 weeks continuous wear and intermittently for one more week (during the night and in vulnerable situations (e.g. when in public environments or any areas the patient feels at risk of injuring their hand)). Patients are advised not to use their hand for any activities. The splint will be custom-made for the individual participant by the treating hand therapist using a thermoplastic material according to standardised RCT protocol.

#### Patients randomised to short splint

The Manchester short splint, or ‘short splint’, is a custom-made, thermoplastic splint which covers the dorsal aspect of the fingers but allows motion at the wrist. The Short splint will be prescribed for 5 weeks continuous wear and intermittently for one more week (during the night and in vulnerable situations (e.g. when in public environments or any areas the patient feels at risk of injuring their hand)). Patients are advised to only use their unaffected fingers for light activities. The splint will be custom-made for the individual participant by the treating hand therapist using a thermoplastic material according to standardised RCT protocol.

#### Patients randomised to mini splint

The relative motion flexion splint, or ‘mini splint’, is a custom-made finger-based splint which prevents full extension of the injured fingers but allows the hand and fingers to be used for daily activities with wrist support. The finger element will be worn continuously for 5 weeks and intermittently for one more week (during the night and in vulnerable situations (e.g. when in public environments or any areas the patient feels at risk of injuring their hand)). The wrist element will be worn continuously for the first 3 weeks of splint wear and intermittently for three more weeks (during night and in vulnerable situations, e.g. when in public environments or any areas the patient feels at risk of injuring their hand). The mini splint will be custom-made for the individual participant by the treating hand therapist using a thermoplastic material according to standardised RCT protocol. The wrist element may be an off the shelf wrist brace.

#### All splints

Participants will be consented and randomised during their first-hand therapy appointment post-surgery, and splints will be fabricated and fitted at the same visit by the hand therapist. Hand therapists will be trained in the provision of all three splints prior to commencing the RCT. A video of the fabrication and insertion of the sensors for each splint will be available for all treating therapists to refer to, to aid splint provision.

### Criteria for discontinuing or modifying allocated interventions {11b}

Participants may wish to withdraw from RCT treatment, or there may be a clinical need to withdraw the participant, for example, a serious adverse event which prevents the participant from wearing the splint. Participants will be encouraged to continue taking part in the RCT follow-up. Any changes to the splinting protocol will be recorded.

### Strategies to improve adherence to interventions {11c}

Adherence will be measured using a heat sensor (Orthotimer) inserted into each splint. The sensor will be removed from the splint at the 6-week follow-up visit and sent to Sheffield CTRU where the data will be downloaded. Splint adherence will be calculated as the mean actual time divided by target wear time for the first five weeks of prescribed splint usage. Participants will be aware of the monitor but will not have access to the adherence data.

### Relevant concomitant care permitted or prohibited during the trial {11d}

All participants will receive post-surgical rehabilitation which will be tailored to their needs. All treating therapists will be provided with best practice guidance showing the exercise guidelines to be prescribed. This will include active and passive composite flexion exercises and active interphalangeal extension exercises for all splint groups and wrist/finger tenodesis exercises as appropriate for the short and mini splint groups only.

Any other therapy intervention deemed necessary to manage swelling, stiffness, scar adhesions, and pain would be carried out as per local standard care and recorded in participants’ medical notes.

### Provisions for post-trial care {30}

The majority of participant’s will have completed rehabilitation by the end of their participation in the RCT. Any participants who require further treatment at the end of the RCT will be treated as per standard care.

## Outcomes {12}

### Primary outcome/endpoint

The primary outcome is the mean post-randomisation total score of the Patient-Rated Wrist and Hand Evaluation (PRWHE), measured at 6, 12, 26, and 52 weeks post-randomisation. The PRWHE is a 15-item patient-reported outcome for assessing wrist and hand pain/disability on a scale of 0 to 100 (0 = no pain/disability) [9].

### Secondary outcomes/endpoints

Timepoints for secondary outcome data collection will be consistent with primary outcome data collection.

#### Patient-reported secondary outcomes

Patient Evaluation Measure (PEM)—patient-reported measure of care received, function, pain and wellbeing [10]Work productivity and activity impairment (WPAI) [11]EuroQoL EQ-5D-5L—health status questionnaire used to derive quality-adjusted life years (QALYs) for the cost-effectiveness analysis [12]Details of any litigation/compensation for injuryGlobal rating of health change (general health compared to previous time point) [13]Preferences for splint attributes (stated and revealed) and splint acceptability (see the “Process evaluation” section)

#### Clinical secondary outcome

Active range of movement (AROM) [14]: The AROM of the affected digit(s) will be measured with a finger goniometer according to a standardised protocol. The total active motion (TAM) will be calculated as the total active flexion of the proximal interphalangeal joint (PIPj) and distal interphalangeal joint (DIPj) motion in a composite fist position minus the extension deficit. The Strickland score will then be calculated from this measurement$$\textrm{Strickland}=\frac{\left(\textrm{active}\ \textrm{flexion}\ \textrm{PIPj}+\textrm{DIPj}\right)-\left(\textrm{extension}\ \textrm{deficit}\ \textrm{PIPJ}+\textrm{DIPj}\right)\times 100}{175}$$Grip strength: This will be measured using a GripAble handheld dynamometer [15] using a standardised protocol. Three attempts will be made on each hand, and the average of the three will be recordedSplint adherence: assessed using a temperature sensor in the participants’ splintComplications and adverse events

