#### Sample size {14}

The sample size was calculated using the methodology and formula for repeated outcome measures [16]. We assumed the following: (i) 90% power; (ii) 1.67% two-sided significance level (to allow for three head-to-head comparisons between the three randomised groups); (iii) 1 baseline and 4 repeated assessments at 6, 12, 26, and 52 weeks post-randomisation; (iv) a target difference of 6 points [17, 18] in the post-randomisation mean PRWHE scores between any two of three groups; (v) a standard deviation of 20 points for the PRWHE outcome at each post-randomisation time point [9, 16–18]; (vi) an exchangeable correlation or compound symmetry of 0.50 between the repeated PRWHE assessments at 6, 12, 26, and 52 weeks post-randomisation [9, 18]; (vii) 20% attrition. With these input parameters, 114 participants per group are required (3 × 114 = 342 in total). After allowing for 20% attrition, we propose to randomise 429 participants in a 1:1:1 ratio (143 long splint: 143 short splint: 143 mini splint).

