### Secondary outcomes

The scores on the repeated continuous secondary outcomes (e.g. PEM, EQ-5D-5L, AROM, Grip strength, Splint adherence) will be compared between the randomised groups using a similar longitudinal mixed effects linear regression model as described for the analysis of the primary outcome. Treatment effects for each protocol stipulated follow-up points will also be presented.

Adherence to the randomised splint treatment during the first 6 weeks post-randomisation will be estimated from the heat sensor in the splint. Adherence will be summarised for each randomised group using a variety of summary measures (e.g. mean number of hours per day wearing the splint) and mean adherence compared between the group using a linear regression model. As with the primary outcome, three treatment effect contrasts and their associated confidence intervals will be estimated and reported from the model: (1) long vs short splint, (2) long vs mini splint, (3) mini vs short splint.

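### The printed Strickland formula lacks an outer bracket, so × 100 falls on the extension deficit alone and the formula contradicts the total active motion definition just before it (minor)

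*Protocol article*

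**What the plan says.** The passage is in the protocol article, Outcomes {12}, under Clinical secondary outcome, in the entry for active range of movement (AROM). It takes two steps.

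- **TAM, in words.** Active flexion is summed over the PIPj and the DIPj and is taken "in a composite fist position minus the extension deficit". So the deficit is subtracted once, in degrees, without scaling.
- **The score, from TAM.** "The Strickland score will then be calculated from this measurement". A formula follows. Its numerator is the bracketed flexion sum (PIPj and DIPj), minus the bracketed deficit sum (PIPj and DIPj), × 100. The whole is divided by 175. No bracket encloses the difference.

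The formula appears nowhere else in the article, and there is no worked example. The Secondary outcomes part of the statistical methods gives the analysis: "The scores on the repeated continuous secondary outcomes (e.g. PEM, EQ-5D-5L, AROM, Grip strength, Splint adherence" and similar measures go into a longitudinal mixed model like that for the primary outcome. That list names AROM and does not name the Strickland score. Table 2 schedules range of movement at baseline and at 6, 12 and 26 weeks.

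**The concern.** The prose and the formula describe different quantities. The prose makes the score a function of TAM, so two fingers with the same TAM must get the same score. The printed formula gives the deficit 100 times the weight of flexion, so it cannot be computed from TAM at all.

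The error is in an outcome definition, and a definition is what a database programmer or a replicating analyst would copy. Copied literally, the result would be almost purely a measure of extension deficit, on a scale that is not a percentage. The misplaced weight also falls where the splints may differ. The Background says the short splint is believed to reduce fixed flexion deformities of the interphalangeal joints, and the adverse event section lists such deformity among expected events. A literal coding could therefore alter a comparison between splints, beyond changing its units. AROM also matters because its assessors are blinded, while patients and treating clinicians are not.

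**Working it through.** **Inputs.** F is active flexion summed over PIPj and DIPj, and D is the extension deficit summed over the same joints, both in degrees. The factor 100 and the divisor 175 come from the printed formula. The article gives no distribution of F or D, so all values of F and D below are assumed, for illustration. There is no computed score in the article to reproduce.

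**Two readings.**

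- As printed, with standard precedence: S_printed = (F − 100 × D)/175
- As the prose implies: S_prose = (F − D) × 100/175 = TAM × 100/175

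**Values.**

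| F | D | TAM | S_printed | S_prose |
|---|---|---|---|---|
| 175 | 0 | 175 | 175/175 = 1.00 | 100.0 |
| 175 | 2 | 173 | (175 − 200)/175 = −0.14 | 98.9 |
| 175 | 5 | 170 | (175 − 500)/175 = −1.86 | 97.1 |
| 150 | 10 | 140 | (150 − 1000)/175 = −4.86 | 80.0 |
| 120 | 20 | 100 | (120 − 2000)/175 = −10.74 | 57.1 |
| 90 | 30 | 60 | (90 − 3000)/175 = −16.63 | 34.3 |
| 90 | 0 | 90 | 90/175 = 0.51 | 51.4 |

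**Where the sign changes.** S_printed < 0 when 100D > F, that is, when D > F/100. The threshold is 1.75 degrees at F = 175, 1.2 degrees at F = 120 and 0.9 degrees at F = 90. With D = 0 and F up to 175, S_printed runs only from 0 to 1.

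**Weights.** In S_printed, one degree of deficit moves the score by 100/175 = 0.571 and one degree of flexion by 1/175 = 0.0057, a ratio of 100:1. In S_prose both move it by 0.571, a ratio of 1:1.

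**Test against the prose.** F = 150 with D = 10 and F = 140 with D = 0 both have TAM = 140. S_prose is 80.0 for both. S_printed is −4.86 for the first and 140/175 = 0.80 for the second. The printed expression is therefore not a function of TAM, although the text says the score is calculated from TAM.

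**Ordering.** Fingers can also change rank. F = 175, D = 5 (TAM 170) scores −1.86 as printed, below F = 90, D = 0 (TAM 90) at 0.51. On the prose definition they score 97.1 and 51.4. The literal form is thus not just a rescaling of the intended score.

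**The case against.** The strongest reply is that this is a typographical slip that corrects itself. The sentence before the formula defines TAM correctly and derives the score from it, and of the two readings above only TAM × 100/175 fits. A careful reader recovers the intended rule from the same paragraph. That stands, and it is why the point is minor.

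It also stands that the harm needs a chain of events: the formula is coded literally, the preceding sentence is ignored, and a score of 1.0 for F = 175 with no deficit, with negative scores elsewhere, passes data checking. Values that odd should be noticed.

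The affected outcome is narrow too. The named outcome is AROM, TAM in degrees is correctly defined, and the analysis section does not list the Strickland score by name.

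The reply does not make the formula right. It is an explicit instruction in the Methods, it conflicts with the adjacent text, and no other part of the article corrects it. The bracketing is explicit in the formula markup, so a fault in reading the text is unlikely. Whether the missing bracket is also in the trial's working documents, or arose in preparing the article, cannot be told from what is shown.

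**Conclusion.** The point holds as a minor error of notation in an outcome definition. As printed, the formula is (F − 100D)/175, which contradicts the TAM sentence. If coded literally, F = 175 with no deficit scores 1.0 instead of 100, and any deficit above F/100 degrees gives a negative score. A between-splint comparison of the Strickland score could then be distorted.

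A reader might infer more, and the documents do not support it:

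- **That the formula is the only rule for the score.** It is not; the TAM sentence gives enough to recover the right one.
- **That the trial's scores are or will be wrong.** The database derivation, analysis code and SAP are not shown, and nothing in the article indicates which form they use.
- **That scores would often be negative.** The threshold of under 2 degrees is arithmetic, but how many participants exceed it depends on a distribution of deficits that the article does not give.
- **That AROM as a whole, or the main result, is compromised.** TAM in degrees, the PRWHE primary outcome and the sample size do not use this formula.

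**What to change.** Restate the formula with one outer bracket:

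Strickland (%) = [(active flexion PIPj + DIPj) − (extension deficit PIPj + DIPj)] × 100 / 175,

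or, more simply, Strickland (%) = TAM × 100/175, which ties it to the sentence before.

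Then confirm that the database derivation and the analysis code use this form, and the SAP as well if it carries the formula. A one-row test is enough: F = 150 and D = 10 must return 80.0.

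The cost is one corrected line and a short check of the code. No design feature, data collection or primary analysis changes.
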